### Strategies to improve adherence to interventions

Course participants are motivated to complete the course irrespectively of the setting because it bears ECTS-points for their PhD education and adds to the mandatory number of ECTS-points. Thus, we expect adherence to be the same in both groups. However, we monitor their presence in the course and allocate time during class for testing the short-term outcomes ( motivation, self-efficacy, preference and learning). We encourage and, if necessary, repeatedly remind them to register with Google Scholar for our testing of the long-term outcome (academic achievement).

### Outcomes

Outcomes are related to the Kirkpatrick model for evaluating learning (Fig. 2) which divides outcomes into four different levels; *Reaction* which includes for example motivation, self-efficacy and preferences, *Learning* which includes knowledge acquisition, *Behaviour* for practical application of skills when back at the job (not included in our outcomes), and *Results* for impact for end-users which includes for example academic achievements in the form of scientific articles [18–20].

**Fig. 2 Fig2:**
[figure not shown]
The Kirkpatrick model

### Primary outcome

The primary outcome is short term learning (Kirkpatrick level 2).

Learning is assessed by a Multiple-Choice Questionnaire (MCQ) developed prior to the RCT specifically for this setting (Appendix 4). First the lecturers of the two courses were contacted and asked to provide five multiple choice questions presented as a stem with three answer options; one correct answer and two distractors. The questions should be related to core elements of their teaching under the heading of research training. The questions were set up to test the cognition of the students at the levels of "Knows" or "Knows how" according to Miller's Pyramid of Competence and not their behaviour [21]. Six of the course lecturers responded and out of this material all the questions which covered curriculum of both courses were selected. It was tested on 10 PhD students and within the lecturer group, revised after an item analysis and English language revised. The MCQ ended up containing 25 questions. The MCQ is filled in at baseline and repeated at the end of the course. The primary outcomes based on the MCQ is estimated as the score of learning calculated as number of correct answers out of 25 after the course. A decrease of points of the MCQ in the intervention groups denotes a deterioration of learning. In the MCQ the minimum score is 0 and 25 is maximum, where 19 indicates passing the course.

Furthermore, as secondary outcome, this outcome measurement will be categorized as binary outcome to determine passed/failed of the course defined by 75% (19/25) correct answers.

The learning score will be computed on group and individual level and compared regarding continued outcomes by the Mann–Whitney test comparing the learning score of the online and onsite groups. Regarding the binomial outcome of learning (passed/failed) data will be analysed by the Fisher’s exact test on an intention-to-treat basis between the online and onsite. The results will be presented as median and range and as mean and standard deviations, for possible future use in meta-analyses.

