## Methods

### Trial design

This study protocol covers synchronous online and in-person onsite setting of research courses testing the efficacy for PhD students. It is a two parallel arms cluster randomized trial (Fig. 1).

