### Secondary outcomes

Motivation assessment post course: Motivation level is measured by the Intrinsic Motivation Inventory (IMI) Scale [22] (Appendix 5). The IMI items were randomized by random.org on the 4th of August 2022. It contains 12 items to be assessed by the students on a 7-point Likert scale where 1 is “Not at all true”, 4 is “Somewhat true” and 7 is “Very true”. The motivation score will be computed on group and individual level and will then be tested by the Mann–Whitney of the online and onsite group.

Self-efficacy assessment post course: Self-efficacy level is measured by a single-item measure developed and validated by Williams and Smith [23] (Appendix 6). It is assessed by the students on a scale from 1–10 where 1 is “Strongly disagree” and 10 is “Strongly agree”. The self-efficacy score will be computed on group and individual level and tested by a Mann–Whitney test to compare the self-efficacy score of the online and onsite group.

Preference assessment post course: Preference is measured as part of the general course satisfaction evaluation with the question “If you had the option to choose, which form would you prefer this course to have?” with the options “onsite form” and “online form”.

Academic achievement assessment is based on 24 monthly measurements post course of number of publications, number of citations, h-index, i10-index. This data is collected through the Google Scholar Profiles [24] of the students as this database covers most scientific journals. Associations between onsite/online and long-term academic will be examined with Kaplan Meyer and log rank test with a significance level of 0.05.

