### Sample size

The power calculation is based on the main outcome, theoretical learning on short term. For the sample size determination, we considered 12 available seats for participants in each course. To achieve statistical power, we aimed for 8 clusters in both online and onsite arms (in total 16 clusters) to detect an increase in learning outcome of 20% (learning outcome increase of 5 points). We considered an intraclass correlation coefficient of 0.02, a standard deviation of 10, a power of 80%, and a two-sided alpha level of 5%. The Allocation Ratio was set at 1, implying an equal number of subjects in both online and onsite group.

Considering a dropout up to 2 students per course, equivalent to 17%, we determined that a total of 112 participants would be needed. This calculation factored in 10 clusters of 12 participants per study arm, which we deemed sufficient to assess any changes in learning outcome.

The sample size was estimated using the function n4means from the R package CRTSize [25].

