### Assignment of interventions: allocation

Randomization will be performed on course-level. The courses are randomized by a computer random number generator [26]. To get a balanced randomization per year, 2 sets with 2 unique random integers in each, taken from the 1–4 range is requested.

The setting is not included in the course catalogue of the PhD School and thus allocation to online or onsite is concealed until 3–4 weeks before course commencement when a welcome letter with course information including allocation to online or onsite setting is distributed to the students. The lecturers are also informed of the course setting at this time point. If students withdraw from the course after being informed of the setting, a letter is sent to them enquiring of the reason for withdrawal and reason is recorded (Appendix 7).

The allocation sequence is generated by a computer random number generator (random.org). The participants and the lecturers sign up for the course without knowing the course setting (online or onsite) until 3–4 weeks before the course.

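### Courses are randomized, but the primary outcome, motivation and self-efficacy get Mann–Whitney tests with no cluster term; at the protocol's own ICC the primary test's true error is about 7.1% to 7.6%, not 5%

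*Protocol article*

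**What the plan says.** The protocol article is explicit about the design. Under Trial design: "It is a two parallel arms cluster randomized trial". Under Assignment of interventions: allocation: "Randomization will be performed on course-level". The Sample size section carries this through: "We considered an intraclass correlation coefficient of 0.02", and "we considered 12 available seats for participants in each course". It arrives at 8 clusters per arm, raised to 10 per arm for dropout of up to 2 students per course.

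The analysis text does not follow. Under Primary outcome, the learning score is to be "compared regarding continued outcomes by the Mann–Whitney test comparing the learning score of the online and onsite groups". Under Secondary outcomes, self-efficacy is to be "tested by a Mann–Whitney test to compare the self-efficacy score of the online and onsite group", and motivation is treated alike. Passed/failed gets Fisher's exact test, and academic achievement gets Kaplan–Meier curves with a log-rank test. Table 3 repeats these tests and assigns Fisher's exact test to preference. The Statistical methods section includes every individual with valid data. The multivariate predictor analysis described there has no cluster term either.

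The Primary outcome section also says that scores will be derived for groups as well as for individuals. It does not define the group level and names no test on course-level values.

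**The concern.** A Mann–Whitney test on individual students takes each score as independent. Students on one course run share that run's group dynamics and test session, so their scores may be correlated. The protocol assumes as much when it plans with a positive ICC. If the analysis ignores this correlation, the standard error is too small and a difference between course runs can be reported as a difference between online and onsite settings.

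The missing analysis plan does not settle the matter. The protocol is not silent on the test: it names one for each outcome, and for the primary outcome it does so in both the text and Table 3. The named test conflicts with the unit of randomization and with the power calculation. At stake is the 5% error rate of the trial's confirmatory comparison.

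**Working it through.** **Inputs from the protocol.** Two-sided alpha 5%, power 80%, ICC 0.02, SD 10, difference 5 points, 12 seats per course, 8 clusters per arm before dropout and 10 after, up to 2 dropouts per course (so 10 to 12 completers).

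**Step 1: reproduce the plan's own figure.** Clusters per arm: k = 2 × [SD × (t₀.₉₇₅ + t₀.₈₀) / difference]² × DE / m, with design effect DE = 1 + (m − 1) × ICC and 2(k − 1) degrees of freedom.

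- m = 12: DE = 1 + 11 × 0.02 = 1.22.
- With 14 df the t quantiles are 2.145 and 0.868, sum 3.013.
- k = 2 × (10 × 3.013 / 5)² × 1.22 / 12 = 7.38, rounded up to 8.

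This matches the stated 8 per arm. The planning therefore includes a design effect that the analysis leaves out.

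**Step 2: true error of a test that ignores clustering.** The naive standard error is too small by a factor √DE, so the true two-sided error is 2 × [1 − Φ(1.96 / √DE)].

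- m = 10: DE = 1 + 9 × 0.02 = 1.18, √DE = 1.086, 1.96 / 1.086 = 1.804, error 7.1%.
- m = 12: DE = 1.22, √DE = 1.105, 1.96 / 1.105 = 1.774, error 7.6%.

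ICCs other than 0.02 are not in the protocol and are shown only as a range:

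| ICC | 10 per course | 12 per course |
|---|---|---|
| 0.01 (assumed) | 6.1% | 6.3% |
| 0.02 (protocol) | 7.1% | 7.6% |
| 0.05 (assumed) | 10.4% | 11.5% |
| 0.10 (assumed) | 15.5% | 17.6% |

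**Step 3: check by simulation.** The formula in Step 2 is for means, so the Mann–Whitney test itself was simulated with no true difference: 10 courses per arm, scores rounded and limited to 0–25, assumed mean 17 and SD 4, 10,000 trials per setting (4,000 for Fisher's test).

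| ICC | Mann–Whitney, 10 / 12 per course | Fisher, passed/failed, 10 / 12 per course |
|---|---|---|
| 0.02 | 6.9% / 7.9% | 4.2% / 5.1% |
| 0.05 | 10.1% / 11.3% | 6.2% / 7.0% |
| 0.10 | 15.2% / 16.7% | 9.6% / 10.7% |

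A t-test on the course means rejected in 5.1% (10 per course) and 4.9% (12 per course) at ICC 0.02. The log-rank test was not simulated.

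**Step 4: power of a cluster-level test.** With 10 courses per arm, the effective number per arm is 10 × m / DE.

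- m = 10: 100 / 1.18 = 84.7; SE = 10 × √(2 / 84.7) = 1.54; 5 / 1.54 = 3.25; power on 18 df is about 87%.
- m = 12: 120 / 1.22 = 98.4; SE = 10 × √(2 / 98.4) = 1.43; 5 / 1.43 = 3.51; power is about 91%.

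**The case against.** A reader might infer that every between-arm comparison fails to hold 5%. The figures do not support that. Fisher's exact test is conservative, and at the protocol's ICC its simulated error stays near 5%; a clear excess appears only from an ICC of about 0.05, which is an assumption. For the log-rank test the same variance argument applies in principle, but no error rate was computed.

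The wording about group-level scores could also be read in the plan's favour. If it meant course-level values, a Mann–Whitney test on the 20 course means would be valid. The likelier reading is the trial arms, because the same sentence uses the word for the online and onsite groups. Either way the wording is ambiguous and specifies no course-level test.

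Some features may keep the ICC low. Programme, course management, lecturers and delivery are described as identical in both settings, so lecturers common to all runs would add little variation between runs. Randomization is called stratified, and separate analyses by course type are planned if possible. If course type is balanced between arms, an unstratified test could offset part of the inflation. These points bear on its size, but the protocol does not rely on them to justify the test, and it still plans with an ICC of 0.02.

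Finally, the Sample size section states a total of 112 participants. That total is hard to reconcile with 20 courses of 10 to 12 (200 to 240). Read literally it gives 112 / 20 = 5.6 per course, DE = 1 + 4.6 × 0.02 = 1.092, and an error of about 6.1%, which is smaller but still above 5%.

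**Conclusion.** The concern holds for the Mann–Whitney outcomes, above all the primary one. As written, the analysis contradicts the design and the sample-size assumption. On the protocol's own ICC the excess is moderate: 2 to 3 percentage points above the nominal 5%. It becomes large only if the true ICC is well above 0.02, and nothing in the named test protects against that.

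The result rests on equal course sizes of 10 to 12 and on 10 courses per arm. The simulated figures also depend on the assumed score distribution. For passed/failed, preference and academic achievement, the supported statement is that the named tests have no cluster term, not that their error rates have been shown to exceed 5% at the planned ICC.

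**What to change.** Name a primary analysis that respects course clustering. Either of these would do:

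- a t-test or permutation test on the 20 course means; or
- a linear mixed model for the post-course score with a random intercept for course run, fixed effects for setting and course type, and small-sample degrees of freedom.

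Report the mean difference with its 95% CI. Use the same approach for motivation and self-efficacy. For passed/failed and preference, use a cluster-level analysis or GEE with a small-sample correction. For academic achievement, use a cluster-robust or course-level method. Keep the individual-level Mann–Whitney, Fisher and log-rank results as descriptive only, and replace the ambiguous group-level wording with the level at which each test is done.

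The cost is a change of protocol wording and a few lines of R, best made before the blinded analyst starts. Intervals become slightly wider. No extra courses or data are needed, since the power in Step 4 remains above the 80% target.

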### Secondary outcomes

Motivation assessment post course: Motivation level is measured by the Intrinsic Motivation Inventory (IMI) Scale [22] (Appendix 5). The IMI items were randomized by random.org on the 4th of August 2022. It contains 12 items to be assessed by the students on a 7-point Likert scale where 1 is “Not at all true”, 4 is “Somewhat true” and 7 is “Very true”. The motivation score will be computed on group and individual level and will then be tested by the Mann–Whitney of the online and onsite group.

Self-efficacy assessment post course: Self-efficacy level is measured by a single-item measure developed and validated by Williams and Smith [23] (Appendix 6). It is assessed by the students on a scale from 1–10 where 1 is “Strongly disagree” and 10 is “Strongly agree”. The self-efficacy score will be computed on group and individual level and tested by a Mann–Whitney test to compare the self-efficacy score of the online and onsite group.

Preference assessment post course: Preference is measured as part of the general course satisfaction evaluation with the question “If you had the option to choose, which form would you prefer this course to have?” with the options “onsite form” and “online form”.

Academic achievement assessment is based on 24 monthly measurements post course of number of publications, number of citations, h-index, i10-index. This data is collected through the Google Scholar Profiles [24] of the students as this database covers most scientific journals. Associations between onsite/online and long-term academic will be examined with Kaplan Meyer and log rank test with a significance level of 0.05.

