## Abstract

**Background:**

The disruption of health and medical education by the COVID-19 pandemic made educators question the effect of online setting on students’ learning, motivation, self-efficacy and preference. In light of the health care staff shortage online scalable education seemed relevant. Reviews on the effect of online medical education called for high quality RCTs, which are increasingly relevant with rapid technological development and widespread adaption of online learning in universities. The objective of this trial is to compare standardized and feasible outcomes of an online and an onsite setting of a research course regarding the efficacy for PhD students within health and medical sciences: Primarily on learning of research methodology and secondly on preference, motivation, self-efficacy on short term and academic achievements on long term. Based on the authors experience with conducting courses during the pandemic, the hypothesis is that student preferred onsite setting is different to online setting.

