## Background

Medical education was utterly disrupted for two years by the COVID-19 pandemic. In the midst of rearranging courses and adapting to online platforms we, with lecturers and course managers around the globe, wondered what the conversion to online setting did to students’ learning, motivation and self-efficacy [1–3]. What the long-term consequences would be [4] and if scalable online medical education should play a greater role in the future [5] seemed relevant and appealing questions in a time when health care professionals are in demand. Our experience of performing research training during the pandemic was that although PhD students were grateful for courses being available, they found it difficult to concentrate related to the long screen hours. We sensed that most students preferred an onsite setting and perceived online courses a temporary and inferior necessity. The question is if this impacted their learning?

Since the common use of the internet in medical education, systematic reviews have sought to answer if there is a difference in learning effect when taught online compared to onsite. Although authors conclude that online learning may be equivalent to onsite in effect, they agree that studies are heterogeneous and small [6, 7], with low quality of the evidence [8, 9]. They therefore call for more robust and adequately powered high-quality RCTs to confirm their findings and suggest that students’ preferences in online learning should be investigated [7–9].

This uncovers two knowledge gaps: I) High-quality RCTs on online versus onsite learning in health and medical education and II) Studies on students’ preferences in online learning.

Recently solid RCTs have been performed on the topic of web-based theoretical learning of research methods among health professionals [10, 11]. However, these studies are on asynchronous courses among medical or master students with short term outcomes.

This uncovers three additional knowledge gaps: III) Studies on synchronous online learning IV) among PhD students of health and medical education V) with long term measurement of outcomes.

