The rapid technological development including artificial intelligence (AI) and widespread adaption as well as application of online learning forced by the pandemic, has made online learning well-established. It represents high resolution live synchronic settings which is available on a variety of platforms with integrated AI and options for interaction with and among students, chat and break out rooms, and exterior digital tools for teachers [12–14]. Thus, investigating online learning today may be quite different than before the pandemic. On one hand, it could seem plausible that this technological development would make a difference in favour of online learning which could not be found in previous reviews of the evidence. On the other hand, the personal face-to-face interaction during onsite learning may still be more beneficial for the learning process and combined with our experience of students finding it difficult to concentrate when online during the pandemic we hypothesize that outcomes of the onsite setting are different from the online setting.

To support a robust study, we design it as a cluster randomized trial. Moreover, we use the well-established and widely used Kirkpatrick’s conceptual framework for evaluating learning as a lens to assess our outcomes [15]. Thus, to fill the above-mentioned knowledge gaps, the objective of this trial is to compare a synchronous online and an in-person onsite setting of a research course regarding the efficacy for PhD students within the health and medical sciences:Primarily on theoretical learning of research methodology andSecondly on◦ Preference, motivation, self-efficacy on short term◦ Academic achievements on long term

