### Statistical methods

Data is anonymized and blinded before the analyses. Analyses are performed by a researcher not otherwise involved in the inclusion or randomization, data collection or handling. All statistical tests will be testing the null hypotheses assuming the two arms of the trial being equal based on corresponding estimates. Analysis of primary outcome on short-term learning will be started once all data has been collected for all individuals in the last included course. Analyses of long-term academic achievement will be started at end of follow-up.

Baseline characteristics including both course- and individual level information will be presented. Table 2 presents the available data on baseline.

**Table 2 Tab2:** Baseline patient characteristics of participants

VARIABLES AT COURSE LEVEL		
	Name	Practical Course in Systematic Review Technique in Clinical Research; Getting started: Writing your first manuscript for publication
	Setting	Online; Onsite
	Language	Danish; English
VARIABLES AT INDIVIDUAL LEVEL		
	Sex	Male; Female
	Education prior to PhD study	MD; MSc Public Health; University College + MSc; MSc Other
	Pre-test knowledge scores	0-25

We will use multivariate analysis for identification of the most important predictors (motivation, self-efficacy, sex, educational background, and knowledge) for best effect on short and long term. The results will be presented as risk ratio (RR) with 95% confidence interval (CI). The results will be considered significant if CI does not include the value one.

All data processing and analyses were conducted using R statistical software version 4.1.0, 2021–05-18 (R Foundation for Statistical Computing, Vienna, Austria).

If possible, all analysis will be performed for “Practical Course in Systematic Review Technique in Clinical Research” and for “Getting started: Writing your first manuscript for publication” separately.

Primary analyses will be handled with the intention-to-treat approach. The analyses will include all individuals with valid data regardless of they did attend the complete course. Missing data will be handled with multiple imputation [28]*.*

Upon reasonable request, public assess will be granted to protocol, datasets analysed during the current study, and statistical code Table 3.

**Table 3 Tab3:** Outcome framework, measurements and analyses

**Kirkpatrick**	**Term**	**Outcome**	**Tool**	**Measurement**	**Analysis**
Primary outcome					

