Level 2 (Learning)	Short	Knowledge	Tested MCQ	25 questions with 3 integers	Mann–Whitney
Level 2 (Learning)	Short	Knowledge Passed	Tested MCQ	Binary	Fisher’s exact
Secondary outcomes					
Level 1 (Reaction)	Short	Motivation	Intrinsic Motivation Inventory	12 questions on 7-point Likert scale	Mann–Whitney
Level 1 (Reaction)	Short	Self-efficacy	Williams and Smith	1 question on 10 point Likert scale	Mann–Whitney
Level 1 (Reaction)	Short	Preference	Survey	Binary	Fisher’s exact
Level 4 (Results)	Long	Academic achievements	Google Scholar	Publications, citations, h-index, and i10-index	Kaplan Meyer and log rank test

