### Perspectives with implications for practice

The results of this study may have implications for the students for which educational setting they choose. Learning and preference results has implications for lecturers, course managers and curriculum developers which setting they should plan for the health and medical education. It may also be of inspiration for teaching and training in other disciplines. From a societal perspective it also has implications because we will know the effect and preferences of online learning in case of a future lock down.

Future research could investigate academic achievements in online and onsite research training on the long run (Kirkpatrick 4); the effect of blended learning versus online or onsite (Kirkpatrick 2); lecturers’ preferences for online and onsite setting within health and medical education (Kirkpatrick 1) and resource use in synchronous and asynchronous online learning (Kirkpatrick 5).

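### The only planned test of preference compares the arms, so it shows whether the setting experienced shifts preference but not which setting students prefer

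*Protocol article*

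**What the plan says.** Under Secondary outcomes, preference is one question in the course evaluation, asked after the course in both arms: "If you had the option to choose, which form would you prefer this course to have". The answer is onsite or online. That paragraph names no analysis. Table 3 supplies one, "Fisher’s exact", and lists nothing else for this outcome. Statistical methods adds: "All statistical tests will be testing the null hypotheses assuming the two arms of the trial being equal based on corresponding estimates".

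The protocol says several things about what it wants to learn:

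- Abstract, Background: "the hypothesis is that student preferred onsite setting is different to online setting".
- Background, on experience during the pandemic: "We sensed that most students preferred an onsite setting". The same section lists students' preferences in online learning as the second of its knowledge gaps.
- Background, hypothesis for the trial as a whole: "we hypothesize that outcomes of the onsite setting are different from the online setting".
- Perspectives with implications for practice: "we will know the effect and preferences of online learning in case of a future lock down". That section also says that the learning and preference results bear on which setting course managers should plan.

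**The concern.** For MCQ score, motivation or self-efficacy, comparing the arms answers the question about setting directly. Preference differs because the response itself names a setting. Comparing the arms on it contrasts the share choosing onsite among students taught online with the share among students taught onsite. That is the effect of experience on stated preference. Which setting most students want is a matter of the level of that share, and the planned test carries no information about the level.

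The Discussion reserves comparison with the literature for secondary outcomes that are significant. A strong preference shared by both arms would give a non-significant test and would drop out of that discussion. It could also be misread as showing no preference, when course planners would be looking to this result for guidance.

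**Working it through.** **The plan's own figure.** There is none to reproduce. The protocol gives no expected preference proportion, no ICC for preference and no sample size for this outcome.

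**Inputs.**
- From Sample size: 10 courses per arm, 12 seats per course, up to 2 dropouts per course. This leaves m = 10 students per course, 100 per arm and 200 overall.
- ICC 0.02 is the protocol's value for the MCQ score. I borrow it for preference and extend the range to 0.10 and 0.20 as an assumption.
- The preference percentages are assumptions chosen for illustration.

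**Step 1. What Fisher's exact test returns (two-sided, course ignored).**

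| Prefer onsite, onsite arm v online arm | Simple average | Fisher's P |
|---|---|---|
| 80/100 v 80/100 | 80% | 1.0 |
| 50/100 v 50/100 | 50% | 1.0 |
| 60/100 v 40/100 | 50% | 0.007 |

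The first two rows are opposite answers to the question of which setting students prefer, and the test gives the same result for both. The third row has no overall preference and a small P.

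**Step 2. What an estimate of the level returns for the first row.** The design effect is DE = 1 + (m − 1) × ICC. The standard error is SE = √(p(1 − p) × DE / 200) with p = 0.80. The interval uses t with 20 − 2 = 18 degrees of freedom, critical value 2.101.

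| ICC | DE | SE | 95% CI for the overall 80% |
|---|---|---|---|
| 0.02 | 1.18 | 0.0307 | 73.5% to 86.5% |
| 0.10 | 1.90 | 0.0390 | 71.8% to 88.2% |
| 0.20 | 2.80 | 0.0473 | 70.1% to 89.9% |

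Every interval lies well above 50%.

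**Step 3. The interval within one arm.** With n = 100 and 9 degrees of freedom (critical value 2.262), 80% has a 95% CI of 70.2% to 89.8% at ICC 0.02 and 64.9% to 95.1% at ICC 0.20. Reporting by arm is therefore also informative.

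**Step 4. The third row with course allowed for.** The difference is 0.20 and SE = √(2 × 0.24 × DE / 100). At ICC 0.02, SE = 0.0753, t = 2.66 and P = 0.016. At ICC 0.20, SE = 0.1159, t = 1.73 and P = 0.10. The 0.007 from Fisher's exact test is therefore too small if classmates' answers are correlated.

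**Step 5. Sensitivity to size.** At 56 per arm (half of the 112 participants stated under Sample size), 50/56 preferring onsite in both arms gives Fisher's P = 1.0, and so does 28/56 in both. A split of 39/56 v 17/56 gives P = 0.00006 with exactly 50% overall. The pattern does not depend on the assumed 100.

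**The case against.** A reader might infer that the trial states a hypothesis about which setting students prefer and then leaves it untested. The documents do not support that. The abstract sentence is garbled. It can equally be read as saying that the onsite setting, described in passing as the one students prefer, differs from the online one. That reading matches the undirected hypothesis in the Background, the Interventions section and the opening of the Discussion, and it matches the null set in Statistical methods. On that reading the comparison between arms does address the hypothesis for this outcome.

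A reader might also infer that the 60% v 40% result is a false finding. It is not. It would correctly show that allocation moved stated preference, which is a proper randomised question. Its P value does weaken once course is allowed for (Step 4).

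Two further objections have force. The remarks in the Background and the Perspectives section are motivation and implication, and neither specifies an analysis. Also, the counts in each arm have to exist before Fisher's exact test can be run, so an 80% preference in both arms would be visible if they are reported. The data are not lost, and a condensed article need not list every descriptive table.

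What stands against this is that the one analysis the protocol does fix for preference does not answer a question it says the trial will inform. The protocol nowhere separates the two questions.

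**Conclusion.** The point holds in a limited form. The planned analysis of preference tests whether the setting experienced changes stated preference. It cannot show which setting is preferred, and the abstract leaves unclear which of the two is meant. Under the assumptions above, 80% preferring onsite in both arms gives P = 1.0, while the overall percentage excludes 50% by at least 20 percentage points across ICC 0.02 to 0.20.

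That the test cannot see the level of preference follows from its null and rests on no assumption. The sizes rest on assumed percentages, an assumed 100 per arm, and an ICC that the protocol does not give for preference. The point concerns one secondary outcome. It does not touch the primary analysis and does not make the randomised comparison wrong.

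**What to change.** 1. In the abstract and in the preference paragraph of Secondary outcomes, say in plain terms whether the question is which setting students prefer, whether experience of a setting shifts preference, or both.
2. In that paragraph and in Table 3, add the percentage preferring onsite in each arm and overall. Take the overall figure as the simple average of the two arm percentages. Give each a 95% CI that allows for clustering by course, and compare it with 50%.
3. Keep the randomised online-versus-onsite comparison as a separately worded question on whether experience shifts preference. Analyse it with a method that allows for course instead of Fisher's exact test.

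The overall average should be added alongside the randomised comparison and should not displace it. Because the item is asked after the course, the average describes a half-online, half-onsite group, and where the arms differ the percentages by arm should be read first.

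The cost is one extra estimate from data already collected and a change of wording, recorded as a protocol modification.
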